**Fig. 2 Fig2:**
[figure not shown]
Timeline of the study indicating enrollment and follow-up as well as timing of laboratory tests, MRI, and echocardiographic imaging modalities

### Statistical analysis

Statistical methodology as published previously by Pätilä et al. [28] will be utilized. Briefly, the Mann-Whitney *U* test will be used for non-parametric continuous variables and results will be reported as median with interquartile range (IQR). Categorical variables will be analyzed using Fisher’s exact test. Intra-observer variability will be assessed using the Bland-Altman method. Testing for *p* values will be carried out two-sided with *p* < 0.05 considered statistically significant. Results should be treated as preliminary due to the small sample size and will be presented with 95% confidence intervals. A sample size of 26 has been shown to be sufficient in our previous studies to demonstrate safety. Computation will be achieved with PASW Statistics (IBM Inc., Armonk, NY) or equivalent software.

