Cardiac-derived stem cells have higher potential to develop along cardiac lineage [7] and differentiate into cardiac myocytes [12] in vivo than the cells derived from other organs. Cardiac stem cells are self-renewing and multipotent, and they have high capacity to form clones and also enhance the differentiation of other progenitor cells to e.g. endothelial and smooth muscle cells. At least six types of stem cells have been isolated and characterized from the heart: Sca-1 cells [13], c-kit cells [14], islet-1 cells [15], cardiac side population cells [16], cardiosphere-derived cells [17], and ALDH(+) (aldehyde dehydrogenase) cells [18]. Cardiac stem cells can be found in abundance in the right atrial appendage [18, 19, 20] which thus represents an appealing source of tissue for cell therapy use.

The efficacy of cell therapy is decreased by the high rate of cell apoptosis soon after the transplantation. Numerous studies have focused on the different routes of the cell delivery. The most investigated approaches are intracoronary and intramyocardial injections and epicardial delivery. Animal models have proven the epicardial delivery to have advantages in securing adequate cell engraftment when compared to any kind of cell injections [21, 22].

Overall, cell-based therapies (by any delivery route) are regarded as safe to the patients [23]. For example, they have been shown to improve left ventricular function [23–26], quality of life, and physical activity tolerance [23, 25, 27]. However, further evidence on safety and feasibility of the epicardial delivery of cardiac stem cells is required.

The primary objective of this trial is to evaluate the clinical feasibility of intraoperative harvesting, processing, and transplantation of autologous atrial appendage tissue micrografts in terms of success in completing the delivery of the transplant to the myocardium in conjunction with cardiac surgery in the operating room as well as in terms of time restrictions associated with both transplant processing and cardiac surgery. Our primary objectives, in terms of safety, are to evaluate acute and 6-month cardiovascular parameters including rhythm, cardiac function, and need for vasoactive or inotropic medication. Our secondary objective is to obtain an initial insight into the therapeutic effect of atrial appendix micrograft transplantation as measured by baseline and 6-month follow-up cardiac functional MRI.

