## Methods/design

### Patient selection

In all, 26 patients from the Helsinki University Hospital, Finland, will be recruited to the study in chronological order by the head researcher. Similar to our previous clinical cell therapy trial [28–31], patients of either gender will be initially evaluated for participation by the cardiologists. Patients with heart failure and scheduled for elective CABG are considered eligible for participation in the trial if they meet the inclusion criteria. The criteria for inclusion and exclusion of the patients are presented in Table 1. The first six patients will be recruited to the atrial appendage-derived cell (AADC) arm. Each patient is given both oral and written information about the trial, and the patient’s written informed consent is required for participation and obtained by the head researcher. After scheduling to surgery, patients will undergo a period of at least 4 to 8 weeks for optimization of drug therapy while waiting for the elective operation.

**Table 1 Tab1:** Inclusion and exclusion criteria for patients enrolled in the study

Criteria for eligibilty
Inclusion criteria
1 Stable coronary artery disease filling the criteria for bypass surgery 2 Age between 18 and 75 years 3 Informed consent obtained 4 LVEF between ≤ 45 and ≥ 20% 5 NYHA class II–IV heart failure symptoms
Exclusion criteria
1 Heart failure due to LV outflow tract obstruction 2 History of life-threatening ventricular arrhythmias or resuscitation, a condition possibly repeating, or an implantable cardioverter-defibrillator 3 Stroke or other disabling condition within 3 months before screening 4 Severe valve disease or scheduled valve surgery 5 Renal dysfunction (GFR < 84 ml/min/1.73 m) 6 Other disease limiting life expectancy 7 Contraindications for coronary angiogram or MRI 8 Participation in some other clinical trial

*LVEF* left ventricular ejection fraction, *NYHA* New York Heart Association, *LV* left ventriculum, *GFR* glomerular filtration rate

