Echocardiography (ECHO), quality of life (QoL) questionnaire (standardized SF-36 health survey questionnaire), New York Heart Association (NYHA) class, basic laboratory tests, and N-terminal pro-B-type natriuretic peptide (NT-proBNP) from blood are all evaluated at baseline as well as at 3 and 6 months of the follow-up. Blood RNA and EDTA plasma samples are taken at the pretrial and at 6 months of the follow-up to search markers for prognostic factors. Cardiac MRI is performed at the pretrial and at 6 months of the follow-up.

To determine the safety of the procedure, the next 20 patients who meet the same inclusion and exclusion criteria and are scheduled for elective CABG operation are recruited to the study as control patients. These patients are treated according to the normal hospital protocol, without the extracellular matrix (ECM) sheet and any additional imaging, examination, or blood tests required for the AADC therapy group. Written consent is obtained also from the control patients.

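### Only independent-group tests are named, but the MRI outcomes exist only as paired values in the six treated patients, and their change cannot isolate the micrografts

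*Protocol article*

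**What the plan says.** All references are to the protocol article.

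- **Groups (Patient selection).** "The first six patients will be recruited to the atrial appendage-derived cell (AADC) arm". The controls follow them: "To determine the safety of the procedure, the next 20 patients" meeting the same criteria are recruited. They receive usual care "without the extracellular matrix (ECM) sheet and any additional imaging, examination, or blood tests required for the AADC therapy group".
- **MRI schedule (Patient selection).** "Cardiac MRI is performed at the pretrial and at 6 months of the follow-up". The sentence names no group, but the control-group rule excludes additional imaging.
- **Tests (Statistical analysis).** The section points to an earlier publication and summarises it. For continuous outcomes it names Mann-Whitney U, a rank method for two groups; this "test will be used for non-parametric continuous variables and results will be reported as median with interquartile range (IQR"). Fisher's exact test is the method named for categorical outcomes. Two-sided p below 0.05 counts as significant, and 95% confidence intervals are promised. No within-patient method is named.
- **Secondary objective (Background).** The aim is to "obtain an initial insight into the therapeutic effect of atrial appendix micrograft transplantation as measured by baseline and 6-month follow-up cardiac functional MRI".
- **Secondary outcomes (End-point measures, Table 2).** Four MRI items, then NT-proBNP, NYHA class, days in hospital and quality of life. The text below the table adds local changes on echocardiography.

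**The concern.** Two things do not fit together.

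**Test and data.** A Mann-Whitney or Fisher test needs two independent groups. For the MRI outcomes there is one group, measured twice. An analyst following the section literally can either run no test or compare the six baseline values with the six 6-month values as if they came from twelve people. For NYHA class, if it is recorded only in treated patients, Fisher's test would ignore both the pairing and the order of the classes.

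**Objective and design.** The objective speaks of an effect of the micrografts. Every treated patient also has bypass grafting and receives the matrix sheet. A before-after change contains all of these, plus any regression to the mean.

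At stake is what the secondary results can mean: a p-value from an unsuitable test, or an improvement read as a micrograft effect when surgery alone could have produced it.

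**Working it through.** **Inputs from the article:** 6 treated, 20 controls; MRI at baseline and 6 months; two-sided 0.05. The stated total is 6 + 20 = 26. It is justified by earlier studies and for safety only. No effect size, SD, correlation or power is given, so there is no power figure to reproduce. **Assumed inputs:** within-patient correlation rho of 0.5 to 0.8; changes in SD units; normal data.

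**1. Which outcomes have a second group?**

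| Outcome | Recorded in controls? |
|---|---|
| MRI: wall thickness, scar, LVEF, wall movement and diastolic function | No (additional imaging excluded) |
| NT-proBNP | No study sample (additional blood tests excluded) |
| Echocardiography at 3 and 6 months, NYHA, SF-36 | Not stated; absence is an inference |
| Routine perioperative safety measures, days in hospital | Can be available in both groups |

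For MRI the comparison is 6 against 0. There is one possible rank arrangement, so no Mann-Whitney p-value exists.

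**2. Cost if baseline and 6 months are treated as independent.** With SD s at each time and n = 6:

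- SE ignoring pairing: s√(2/n)
- Correct SE: s√(2(1−rho)/n)
- Ratio: 1/√(1−rho)

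Power is for a true change of 1 SD of a single measurement. Mann-Whitney and paired t are simulated with bivariate normal data, 20,000 runs. The signed-rank test at n = 6 is significant only if all six changes have the same sign, so its power is Φ(1/√(2(1−rho)))⁶; the opposite direction adds a negligible amount.

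| rho | SE ratio | Mann-Whitney 6 v 6 | Signed-rank | Paired t |
|---|---|---|---|---|
| 0.5 | 1.41 | about 27% | 35% | 51% |
| 0.7 | 1.83 | about 27% | 54% | about 72% |
| 0.8 | 2.24 | about 27% | 70% | 87% |

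With no true change, the misapplied Mann-Whitney test rejects in about 1% of trials at rho 0.5 and 0.1% at rho 0.8, instead of about 5%.

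**3. Limits of a paired test in six patients.** The smallest two-sided signed-rank p is 2/2⁶ = 0.031 with six pairs and 2/2⁵ = 0.0625 with five. One missing 6-month MRI therefore makes significance impossible with that test. The half-width of a paired 95% interval is 2.571/√6 = 1.05 SD of the change.

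**4. Attribution.** Suppose the micrografts do nothing and the other components give a mean change of 0.5, 1.0 or 1.5 SD of the change (assumed). A paired t-test with n = 6 is then significant for improvement in 17%, 51% or 83% of trials (noncentral t, 5 degrees of freedom). Choosing the correct paired test does not cure this.

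**The case against.** - **The tests are a summary.** The section abridges an earlier publication that is not at hand, and a paired method may be described there. No sentence assigns Mann-Whitney or Fisher to the MRI outcomes. A charitable reading is two-group tests for safety, where the controls belong, and description within the treated group for MRI. This stands in part: a reader might infer that the plan will run Mann-Whitney on baseline against 6 months and report over-wide intervals, but the article does not say so. The figures in step 2 of the working apply only if that is done. What remains is that the text names only tests that do not fit these outcomes, and a paired method would not repair the attribution.
- **Control measurements are not fully specified.** A reader might infer that controls lack every secondary outcome. Only imaging and blood tests are clearly excluded. SF-36 falls under the exclusion only if a questionnaire counts as an examination, and NYHA class may be recorded routinely. The article says that Figure 2 gives timings for each patient, and that figure is not shown.
- **The power loss varies.** The contrast with the signed-rank test is large at rho 0.8 and small at rho 0.5 (27% against 35%).
- **Drug optimisation.** A reader might add this as a second confounder between the two scans. The article places it before surgery and its text gives no date for the baseline MRI, so the overlap is unproven.
- **The claim is hedged.** The article promises an initial insight, labels the MRI outcomes preliminary efficacy, and leaves efficacy to later trials, where a matrix-only placebo will be considered. It does not announce that any improvement will be credited to the transplant. But the word preliminary is tied to small sample size, and the limitations listed in the Discussion (allocation, single centre) omit the missing imaging comparator.

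**Conclusion.** The point holds for the MRI outcomes and study NT-proBNP, and for any other outcome that proves not to be recorded in controls. For these the named tests either have no second group or would ignore pairing. In the second case the SE of the change is inflated 1.4 to 2.2 times, and power for a 1 SD change is about 27% instead of 35% to 70% (signed-rank) or 51% to 87% (paired t). These sizes rest on assumed correlations of 0.5 to 0.8 and normal data.

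Independently of the test, the objective of insight into a micrograft effect is not supported, because the change after surgery includes bypass grafting and the matrix sheet.

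This should be fixed but does not undermine the trial. These are secondary outcomes, and the Discussion judges success on the primary safety and feasibility measures. The two-group tests remain usable for outcomes recorded in both groups.

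**What to change.** 1. In Patient selection, state which assessments controls receive and when, in particular echocardiography at 3 and 6 months, NYHA class and SF-36.
2. In Statistical analysis, limit Mann-Whitney and Fisher to outcomes recorded in both groups, such as the perioperative safety measures and days in hospital.
3. For outcomes recorded only in treated patients, show each patient's change and the paired change with a 95% confidence interval (paired t, or Hodges-Lehmann with signed-rank). Use a shift table for NYHA class. Note that signed-rank cannot reach p below 0.05 with five pairs.
4. Reword the secondary objective along these lines: *to describe change from baseline to 6 months after CABG plus micrograft transplantation; the contribution of the micrografts cannot be separated.*

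The cost is analysis and objective wording only, with no added patients or visits. The downside is that the efficacy objective becomes descriptive. Imaging the controls would add a comparator at the price of extra scans. Because controls have no matrix sheet and are enrolled after the treated patients, it would still not isolate the micrografts.

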### End-point measures

Table 2 lists the outcome measures of the trial. Specifically, the primary outcome measures are patient safety in terms of hemodynamic and cardiac function and feasibility of the therapy administration in a clinical setting. Hemodynamics is evaluated during the operation and stay at the intensive care unit (ICU) by the need for vasoactive medication and success of weaning from cardiopulmonary bypass and respirator. Postoperative hemodynamic criteria for assessing safety are cardiac index, hemoglobin, SvO_2_, serum potassium level, and blood glucose level. Cardiac function is evaluated also during the operation by transesophageal ECHO and during the stay at ICU by transthoracical ECHO as well as telemetric monitoring of rhythm. Feasibility is evaluated by the success in completing the delivery of the cell sheet to the myocardium, waiting times in minutes for either the cell sheet or the heart after finishing anastomoses, and the success in closing the right atrial appendage by purse string suture without additional sutures or patching.

**Table 2 Tab2:** Primary and secondary outcome measures

Primary outcome measures	Secondary outcome measures
Safety	Preliminary efficacy
For assessing hemodynamics during the operation and at the intensive care unit	For assessing cardiac function and remodeling as measured by MRI
1. Need for vasoactive medication	1. Left ventricular wall thickness
2. Cardiac index in l/min/m^2^	2. Change in the amount of myocardial scar tissue
3. Hemoglobin in g/l	3. Change in left ventricular ejection fraction
4. Oxygen saturation in the pulmonary arterial blood (SvO_2_) in %	4. Change in movement and diastolic function of left ventricular wall
5. Serum potassium level in mmol/l	Others
6. Blood glucose level in mmol/l	1. Plasma concentrations of N-terminal pro-B-type natriuretic peptide (NT-proBNP) levels
For assessing cardiac function during and after the operation by echocardiogram	2. New York Heart Association class
7. Left ventricular ejection fraction (EF) in %	3. Days in hospital
8. Pericardial effusion in mm	4. Changes in the quality of life measured by questionnaire
For assessing cardiac function after the operation	
9. Telemetric monitoring of rhythm	
Feasibility	
1. Success in completing the delivery of the transplant to the myocardium	
2. Waiting time in minutes for the finished transplant to be placed on the myocardium after doing all the required anastomoses	

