The purpose of this study is to address patient safety and clinical feasibility of the therapy. We will determine the success of this trial based on the primary outcome measures. If the therapy is proved to be safe without any disturbances in patients’ cardiac rhythm, hemodynamics, and cardiac function and the method can be successfully performed simultaneously with bypass surgery, the results of this trial are then further evaluated in succeeding trials for transplant’s therapeutic efficacy. Double-blind randomization and placebo control using the matrix sheet with and without the micrografts will be considered for our future studies.

Our interests has also been combining stem cell therapy with gene therapy and using autologous minimally manipulated micrografts in conjunction with CABG surgery [47–49]. By administrating genetically modified transplanted cells, we are able to repair also faulty genetic tissue of the heart [47]. Even though cell therapy has promising results, studies regarding safety and clinical efficacy require further investigation.

This study on feasibility and safety of autologous atrial micrograft epicardial transplantation has some limitations. The allocation is not randomized, and the patients are recruited to the groups in chronological order. Also, this trial is carried out as a one-center trial, and therefore, the number of eligible patients is small. Although randomization does not occur, we have considered that no selection bias will take place due to low number of patients and because all patients who are eligible and give their consent are included in the study.

In conclusion, given the severe problems associated with heart failure and its increasing high prevalence [50] in the elderly population, it is of utmost importance to devise effective novel evidence-based cell therapies. Epicardial delivery of AADCs with ECM cells represents a novel approach to restore the cellular loss of infarcted myocardium. We believe that AADC therapy administered during CABG surgery will have impact on patient treatment in the future.

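### The plan as read makes no use of pre-operative LVEF when the primary safety LVEF is compared between two small, non-randomised arms; the comparison should be baseline-adjusted

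*Protocol article*

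**What the plan says.** - **Outcome.** Table 2 (End-point measures) lists among the primary safety measures, by echocardiogram during and after the operation, "7. Left ventricular ejection fraction (EF) in" per cent. The secondary MRI list in the same table has "3. Change in left ventricular ejection fraction".
- **Test.** Statistical analysis refers to the methods of an earlier publication and then summarises them. The Mann-Whitney U test "will be used for non-parametric continuous variables and results will be reported as median with interquartile range (IQR"). Testing is two-sided at 0.05, with 95% confidence intervals, and results are to be treated as preliminary. No other between-group test for continuous data is named, and no baseline term.
- **Entry value.** Table 1 (Patient selection) requires "4 LVEF between ≤ 45 and ≥ 20" per cent. The controls are "the next 20 patients who meet the same inclusion and exclusion criteria", so a qualifying LVEF is needed in both arms.
- **Imaging in controls.** They are treated by normal hospital protocol, without "any additional imaging, examination, or blood tests required for the AADC therapy group".
- **Allocation.** The first six patients receive the graft. The Discussion says: "The allocation is not randomized, and the patients are recruited to the groups in chronological order". It adds that selection bias is not expected, partly because the number of patients is low.

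**The concern.** The control group is there to judge safety, and the Discussion ties the success of the trial to the primary outcomes, cardiac function among them. Entry allows LVEF to span 25 points. Neither randomisation nor matching balances it, and low numbers make a chance imbalance larger rather than smaller.

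If post-operative LVEF is compared as a level, part of any difference between 6 and 20 patients reflects the hearts they started with. A weaker starting group can look like harm from the graft, and a stronger one can conceal a real fall. The value needed to separate the two is already an entry requirement.

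**Working it through.** **The plan's own figure.** The article says that 26 patients suffice to demonstrate safety. This cannot be reproduced, because no effect size, SD, power or margin is given.

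**Inputs from the article.** 6 treated, 20 controls, two-sided 0.05, entry LVEF 20-45%.

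**Assumptions.** Baseline LVEF spread evenly over 20-45% gives SD = 25/√12 = 7.22 points; 5 and 9 points are shown as a range. The correlation (rho) of pre- and post-operative LVEF is not given; 0.3 to 0.8 is used.

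**Step 1: chance baseline gap.** SE of the difference in mean baseline = SD × √(1/6 + 1/20) = 0.4655 × SD.

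| SD (points) | SE | 95% range | P(gap at least 5 points) |
|---|---|---|---|
| 5 | 2.33 | ±4.6 | 3% |
| 7.22 | 3.36 | ±6.6 | 14% |
| 9 | 4.19 | ±8.2 | 23% |

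A baseline gap carries over to follow-up as roughly rho × gap. At rho 0.6 a 5-point gap gives 0.6 × 5 = 3 points of difference that the graft did not cause.

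**Step 2: consequence when a gap has occurred.** Simulation of 20,000 trials per setting, uniform baseline, outcome SD 7.22, exact Mann-Whitney on the level against ANCOVA. Entries are the share of trials with p < 0.05, raw / ANCOVA.

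| rho | No effect, treated arm starts more than 5 points lower | True 5-point harm, treated arm starts more than 5 points higher |
|---|---|---|
| 0.3 | 6% / 5% | 12% / 28% |
| 0.5 | 12% / 5% | 5% / 33% |
| 0.6 | 14% / 5% | 3% / 41% |
| 0.7 | 19% / 4% | 1% / 47% |

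Over all trials with no true effect, the raw test rejects in 4-5%, so its overall level is intact when the arms are exchangeable.

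**Step 3: power over all trials.** Adjustment cuts the residual variance by rho²: 9%, 25% and 49% at 0.3, 0.5 and 0.7. For a 1.0 SD effect (7.2 points at SD 7.22), with bivariate normal data, separate simulation runs gave:

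| rho | Mann-Whitney | Rank ANCOVA | ANCOVA |
|---|---|---|---|
| 0.3 | 48-50% | 52-53% | 55-57% |
| 0.5 | 48-50% | 58-60% | 63-65% |
| 0.7 | 48-50% | 73% | 80% |

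For a 5-point harm at SD 7.22, raw against ANCOVA is 27% v 31% (rho 0.3), 27% v 37% (0.5), 26% v 50% (0.7) and 26% v 64% (0.8). At rho 0 it is 26% v 28%, so about 2 points of ANCOVA's advantage come from normal-theory testing of normal data and not from the baseline.

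**Step 4: change scores.** Mann-Whitney on the change from baseline, for the same 5-point harm, has power 20% (rho 0.3), 27% (0.5), 32% (0.6) and 57% (0.8). It beats the raw test only above a correlation of about 0.5.

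**The case against.** - **The raw level is inferred.** A reader might take the article to state that post-operative LVEF is tested as a raw level. No sentence says so. Table 2 gives units for its safety measures, the abstract speaks of cardiac function over time, and Mann-Whitney could be run on changes. This stands, so the point is about the plan as read. That reading is still the natural one: the same table uses the word change for the secondary LVEF and not for the primary.
- **The article is a summary.** It defers to earlier methods and ties Mann-Whitney to non-parametric variables, so details may lie elsewhere. That is fair for details, but the article does name a method, and the point is that a better one is available for this design.
- **Chance imbalance is not bias.** A reader might infer that the 5% error rate is inflated overall. It is not, if the arms are exchangeable, and a valid 95% CI allows for chance imbalance. The error is conditional on the gap. Sequential allocation does not guarantee exchangeability, but the figures above do not measure any systematic difference.
- **Adjustment is not free.** Controls get no additional imaging, criterion 4 names no modality or date, and at least 4 to 8 weeks of drug optimisation precede surgery. Baseline may therefore be measured differently or at a different time in the two arms. This stands and shapes the fix.
- **Small role.** LVEF is one of nine listed safety measures, results are called preliminary, and the lack of randomisation is acknowledged. This argues against treating the point as critical, not against a better comparison.

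**Conclusion.** The point holds in this form: the plan as read leaves the required pre-operative LVEF out of a non-randomised 6 v 20 comparison of a primary safety measure, and adjusting for it is the better analysis. It should be changed, but it does not invalidate the trial.

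The size rests on assumptions. A chance gap of at least 5 points in mean baseline LVEF has probability 3-23% for an SD of 5 to 9 points. The power gain for a 1.0 SD effect is a few points at a correlation of 0.3 and about 25-30 points at 0.7.

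Two further readings go beyond the documents. One is that adjustment would cure the lack of randomisation: it deals with LVEF only, and other differences between the first 6 and the next 20 patients remain. The other is that it would make 26 patients adequate: for a 5-point harm, adjusted power is still only 31-64% at correlations of 0.3 to 0.8.

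**What to change.** State in Statistical analysis that the primary LVEF comparison is adjusted for the last pre-operative LVEF, by ANCOVA or by rank ANCOVA (ranks of post-operative LVEF regressed on ranks of pre-operative LVEF, residuals compared between arms). Choose one in advance. Report the adjusted difference with its 95% CI; with rank ANCOVA, whose result is on the rank scale, take the difference in LVEF points from the ANCOVA model. Keep Mann-Whitney on the level as a supporting analysis. Do not make a simple change score the main analysis, since it loses power at low correlation.

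Record the modality and date of the pre-operative LVEF in each arm, and use the same modality in both where routine data allow.

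Cost: a few sentences, some recording work in the controls and one degree of freedom. Linearity and equal slopes can hardly be checked with 6 treated patients, and correction is only partial if baseline is measured differently by arm.

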3. Waiting time in minutes for the heart after doing all the anastomoses and before the transplant is finished	
4. Closing the right atrial appendage after removing the standardized tissue piece for preparing the transplant	

The secondary outcome measures are change in LV wall thickness and movement and diastolic function as measured by MRI, change in the amount of myocardial scar tissue as measured by MRI, local changes in systolic and diastolic measures as estimated by ECHO, changes in left ventricular ejection fraction (LVEF), pro-BNP level, NYHA class, hospitalization or the days in hospital, and QoL.

Figure 2 presents the timeline of the study indicating enrollment and follow-up as well as timing of laboratory tests, MRI, and echocardiographic imaging for each patient.

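### NYHA class is an ordered secondary outcome, but the only test the plan names for categorical variables is Fisher's exact test, which ignores the order: valid, but less efficient for a shift in one direction

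*Protocol article*

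**What the plan says.** Under Statistical analysis, the protocol article states that "the Mann-Whitney *U* test will be used for non-parametric continuous variables" and that "Categorical variables will be analyzed using Fisher’s exact test". It adds: "Testing for *p* values will be carried out two-sided with *p* < 0.05 considered statistically significant". No test is named for ordered categories.

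Table 2, under End-point measures, lists "2. New York Heart Association class" among the secondary outcomes, and the text below the table repeats it in the run "pro-BNP level, NYHA class, hospitalization or the days in hospital, and QoL".

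The groups are unequal. Under Patient selection, "The first six patients will be recruited to the atrial appendage-derived cell (AADC) arm", and the controls are the following 20 eligible patients. The same section has NYHA class assessed at baseline, 3 months and 6 months. It also says that controls follow ordinary hospital care and are spared the extra tests and examinations of the treated group.

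**The concern.** NYHA class runs from I to IV in order of severity. It is a category rather than a continuous measurement, so under the rule as written it falls to Fisher's test. The article never assigns NYHA by name, so this is an inference, but it is the natural one.

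On a table with more than two classes, Fisher's test treats the classes as unordered labels. It ranks tables by their probability alone, so movement of the treated arm in one direction earns no more credit than scatter in both. With six treated patients there is little information to spare, and the plan already contains a rank test that uses the order. At stake is the power of one secondary comparison. Error control and the primary safety and feasibility outcomes are not affected.

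**Working it through.** **The plan's own figure.** The article states a sample size of 26, which is 6 + 20. It gives no power, effect or class distribution for NYHA, so there is no power figure to reproduce.

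**Inputs from the article.** 6 treated and 20 control patients; two-sided p < 0.05; Fisher's exact test for categories; Mann-Whitney available in the plan.

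**Assumptions, not in the article.** Control class distributions as listed in the table below. A proportional-odds shift: for each class j, the odds of being in class j or better are multiplied in the treated arm by a common odds ratio (OR). A worsening uses 1/OR. All 20 controls are taken to have a recorded class.

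Example of the shift: controls 25/50/25% over three classes have cumulative proportions 0.25 and 0.75, so odds 1/3 and 3. With OR 5 the odds become 5/3 and 15, the cumulative proportions 0.625 and 0.9375, and the treated distribution 62.5/31.25/6.25%.

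**Method.** All possible tables for 6 v 20 were enumerated. For each, two exact p-values were computed from the conditional distribution given the class totals: Fisher's test on the full table (sum over all tables no more probable than the one seen), and Mann-Whitney with mid-ranks (sum over all tables whose treated rank sum lies at least as far from its expectation). Power is the total probability of tables with p < 0.05.

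**One table by hand.** Treated 0/1/3/2 and controls 4/9/6/1 over classes I to IV; class totals 4/10/9/3.
- Ways to choose the treated six: C(26,6) = 230,230. Ways giving this table: C(4,0) × C(10,1) × C(9,3) × C(3,2) = 1 × 10 × 84 × 3 = 2,520.
- Fisher: tables with at most 2,520 ways add up to 33,400, so p = 33,400/230,230 = 0.145.
- Mann-Whitney: mid-ranks are 2.5, 9.5, 19 and 25. Treated rank sum = 9.5 + 3 × 19 + 2 × 25 = 116.5; expected 6 × 27/2 = 81; distance 35.5. Tables at least that far away add up to 7,245, so p = 7,245/230,230 = 0.031.

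This table was picked to show the two tests parting. It says nothing about how often they do.

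**Power (%), Fisher / exact Mann-Whitney (gain in points, from unrounded values).**

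| Control distribution (%), direction | OR 3 | OR 5 | OR 10 |
|---|---|---|---|
| 20/45/30/5, better | 11.9 / 19.4 (7.5) | 22.7 / 37.1 (14.5) | 43.4 / 63.6 (20.2) |
| 20/45/30/5, worse | 14.1 / 20.3 (6.3) | 26.5 / 38.8 (12.3) | 49.8 / 66.7 (16.9) |
| 10/40/40/10, either | 12.9 / 19.7 (6.7) | 24.2 / 37.8 (13.6) | 47.0 / 66.0 (19.0) |
| 35/45/18/2, better | 9.6 / 16.0 (6.4) | 17.9 / 29.6 (11.7) | 32.6 / 49.7 (17.1) |
| 35/45/18/2, worse | 17.0 / 20.8 (3.8) | 31.3 / 39.7 (8.5) | 55.9 / 68.0 (12.1) |
| 25/50/25, either | 12.6 / 18.2 (5.6) | 24.0 / 34.9 (10.8) | 44.8 / 59.7 (14.9) |
| 10/40/50, worse | 6.7 / 9.4 (2.7) | 10.7 / 16.0 (5.3) | 16.3 / 25.1 (8.7) |
| 10/40/50, better | 19.5 / 20.5 (1.0) | 35.5 / 38.9 (3.4) | 61.6 / 66.7 (5.1) |

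The gains lie within about 2 to 8 points at OR 3, 4 to 15 at OR 5 and 5 to 20 at OR 10. The last row, the most skewed, falls just under the first two ranges.

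**Wider set.** Ten control distributions (five with three classes, five with four) at OR 3, 5, 8, 12 and 20 make 50 scenarios. The exact Mann-Whitney test is the more powerful in all 50, by 1.0 to 26.9 points.

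**Validity.** With no effect, the same ten distributions give rejection rates of 4.0 to 4.5% for Fisher and 3.4 to 4.3% for the exact Mann-Whitney test.

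**The case against.** The strongest reply is that this is a preference about efficiency in a small study. Fisher's test keeps its error rate, NYHA is one of several secondary outcomes, success is judged on the primary outcomes, and results are declared preliminary. The statistics paragraph is also a summary of methods published for an earlier trial, which may handle NYHA in its own way. All of this stands, and it keeps the point minor. It does not remove it: the article states a positive rule for categorical variables, and that rule suits an ordered scale poorly.

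Fisher's test is also the stronger of the two when the difference has no direction. With controls 25/50/25% and treated 50/0/50%, its power is 57.2% against 14.0%. That is a real, if less likely, trade-off.

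Four stronger readings are tempting, and the article does not support them:
- *A reader might infer that a shift would as a rule be missed by Fisher and found by the rank test.* At OR 5 the rank test itself reaches at most about 40% in the table above, and no more than about 18% of trials are significant by the rank test alone.
- *A reader might take one power loss as a property of 6 v 20 patients.* It depends on the class distribution and the effect, neither of which is given. If only two classes occur, the two exact tests coincide (22.6% each in one case, 66.4% in another).
- *A reader might rest the point on baseline NYHA, which every patient has.* Entry requires "5 NYHA class II–IV heart failure symptoms", so class I cannot occur at baseline, and baseline precedes treatment and cannot show its effect.
- *A reader might count the cost of merging classes.* The article proposes no merging.

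**Conclusion.** The point holds as a modest, cheap improvement. As worded, the plan most naturally sends an ordered secondary outcome to a test that ignores its order. The test is valid but gave less power than the exact rank test for every ordered shift examined. The size is conditional on the assumed distributions, the proportional-odds shift and class data on all 26 patients: about 2 to 8 points at OR 3, 4 to 15 at OR 5, 5 to 20 at OR 10, and about 1 to 27 over the wider set at OR 3 to 20.

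The last of these assumptions is not assured. Controls receive no additional examinations, so a follow-up comparison of 6 v 20 exists only as far as routine care records NYHA class in them. With fewer controls the figures above would not apply as they stand.

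**What to change.** In Statistical analysis, replace the sentence on categorical variables by wording to this effect: *Ordinal variables (NYHA class) will be compared on the full scale with the exact Mann-Whitney U test allowing for ties. Nominal and binary variables will be compared with Fisher's exact test. The full distribution of NYHA class will be reported by arm, with the number of controls who have a recorded class.*

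The cost is this wording; no extra patients, visits or data are needed, and the test is already in the plan. The price is lower sensitivity to a difference without direction, which the reported distribution would still let a reader see.
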